### 4.4. Measures of Outcome

The primary outcome measure is patient-reported fatigue. The CIS is a 20-item self-report questionnaire that will be used to evaluate for changes in subjective experience of fatigue severity, and its three related domains of reduction in motivation, reduction in activity, and reduction in concentration (a de facto indicator for mental fatigue). The CIS has been used previously in studies of MD [26]. It has been shown to have good internal consistency (Cronbach’s alpha = 0.90 for total CIS, and between 0.83 and 0.92 for the individual scales) and moderate discriminant validity (CC 0.62) with high test–retest reliability (r = 0.74–0.86) [27,28].

To assess safety, participants will be asked to report/record in a study diary any unexpected effects (suspected side effects or adverse events) during the study. We will ask participants about such matters at each assessment point. Participants will have contact details of the investigators should they experience effects of concern.

Secondary measures will be assessed to aid in determining the feasibility of progressing the work into a group-based study because fatigue in mitochondrial disease is closely related to depression, anxiety, and sleepiness. These measures include the following:
DASS-21 to measure depression, anxiety, and stress (21 questions taking about three minutes to complete). All three scales of the DASS have been shown to have high internal consistency and meaningful discriminations in a variety of clinical and research settings. The short version, DASS-21, will be used in the study as it has shown validity comparable with the long version and will pose a lesser burden to complete for the participants [29].The Epworth Sleepiness Scale (ESS) is a self-administered questionnaire with eight questions. Respondents are asked to rate, on a four-point scale (0–3), their potential for dozing off or falling asleep during eight different activities. The ESS score (the sum of eight item scores, 0–3) can range from 0 to 24. A higher ESS score indicates a greater inclination towards ‘daytime sleepiness’. The questionnaire takes no more than two or three minutes to answer and is available in many languages. The ESS has strong external criterion validity and a high level of internal consistency (Cronbach’s alpha = 0.88) [30].To assess for any change in physical activity level, we will use the self-reported Habitual Activity Estimation Scale (HAES). The questionnaire is used to record time spent during a typical weekday and weekend, being “inactive” (lying down), “somewhat inactive” (sitting), “somewhat active” (standing or walking), and “very active” (sweating or breathing hard). The HAES is suitable for this study as it distinguishes between weight-bearing and non-weight-bearing activities, is feasible in clinical populations, sensitive to change, reliable and valid, has strong agreement with instrumented measures of physical activity, and high utility in a wide age range of free-living clinical populations [31].Blood lactate and CK [32] will be analysed to determine if they are responsive to the intervention. Lactate is a major energy source for mitochondrial respiration thus an indirect indicator of the effect on mitochondrial activity. CK turns creatine into the high-energy molecule phosphocreatine, used by the body to generate energy. Any condition that interferes with muscle energy production or use increases levels of CK in the blood. These blood tests are standard and part of the routine assessment of people with mitochondrial diseases [1]. Blood tests will be required on three occasions, at intake to the study and at the start and end of active intervention Phase C.We will test exercise tolerance on five occasions, using the following measures which focus on the leg muscles receiving the PBM treatment:○The 60 s sit-to-stand (60STS) test: This test is indicative of quadriceps muscle and gluteus muscle strength and endurance. Although it has not been used in mitochondrial disease, the 60STS test is simple and has been found to be sensitive in measuring the efficiency of rehabilitation in other diseases [33]. An improvement of at least three repetitions is consistent with physical benefits.○As the gastrocnemius muscle will be the focus of MR spectroscopy, we will assess calf muscle strength. There is no validated measure of calf muscle strength [34], thus we will use a simple measure of the number of heel raises that can be repeated by participants in 60 seconds.○If the participant uses a smart device (e.g., watch or ring), we will collect data on physical activity (step counts) across each phase of the study to assist in verifying participant activity levels as measured using the HAES.

Some participant medical history will be harvested from patient medical records to assist in confirming illness status for the purposes of potential publication of the N-of-1 trial series. As per CENT2015 [22], we will profile participant age, sex, confirmation of MELAS diagnosis, relevant co-morbidities, and age at MELAS diagnosis.

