## Abstract

**Background**: There is no cure for mitochondrial diseases which manifest in numerous ways including fatigue, muscle weakness, and exercise intolerance. Medical treatment varies and focuses on managing symptoms. Photobiomodulation (PBM) can decrease mitochondrial damage thereby increasing energy production and decreasing cell death. This pilot study will apply PBM to people with mitochondrial encephalomyopathy, lactic acidosis, and stroke-like episodes (MELAS) to examine the safety of application, and if changes occur in symptoms and signs after cross-over application/withdrawal of a sham or active PBM treatment including a two-week period of washout. **Methods**: This study is an exploratory, prospective series N-of-1 (single patient) studies. The protocol is guided by the CONSORT extension for reporting N-of-1 trials (CENT 2015), chosen due to the rarity of mitochondrial diseases, the fluctuating symptomology, and heterogeneity of the clinical presentation. The primary outcome is patient-reported fatigue assessed using the Checklist of Individual Strength and with concomitant evaluation of safety. Secondary measures are of depression, anxiety and stress, sleepiness, physical activity, blood lactate and creatine kinase, physical measures of sit-to-stand, and heel raise capability. Mitochondrial function will be evaluated using hydrogen magnetic resonance spectroscopy for lactate. PBM will be a participant-administered, home-based therapy using a multiple diode flexible array (BeniLight iLED-Pro Multi-Wave Multi-Pulse belt; 465 nm, 660 nm, 850 nm; average irradiance 5.23 mW/cm^2^; total joules: 770.1 J/treatment, all sites; 5 KHz; 20% duty ratio) over the anterior thigh muscles, posterior calf muscles and abdomen for 10 min to each site, three times/week. The safety of the intervention will be assessed. Descriptive statistics, causal analyses of time series data and dynamic modelling will be applied as relevant to the variables collected. Hydrogen magnetic resonance spectra will be acquired and averaged to obtain the content of the targeted hydrogen levels. **Discussion**: The study will provide guidance on whether and how to progress to a larger, randomised cohort study with sham control.

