## 1. Introduction

Primary mitochondrial diseases (MD) are the most common group of inherited metabolic diseases and are characterized by impairment of the mitochondrial electron transport chain. The presentation of MD is complex, and diagnosis can be challenging due to the multi-system nature of these conditions. There is no curative treatment for MD, and management is supportive [1]. Although there are a number of mitochondrial and nuclear pathogenic variants associated with primary mitochondrial disease, the m.3243 A>G mutation in the *MT-TL1* gene encoding the mitochondrial tRNA^Leu(UUR)^ is one of the more common variants identified [2,3], and is associated with two primary, often overlapping syndromes:Mitochondrial encephalomyopathy, lactic acidosis, and stroke-like episodes (MELAS) primarily affect the nervous system and muscles. MELAS presents in children or young adults as recurrent episodes of encephalopathy, myopathy with reduced exercise tolerance and fatigue, migraines, seizure disorder, and focal neurological deficits.Maternally inherited diabetes and deafness (MIDD) is characterised by mitochondrial diabetes, hearing impairment, and maculopathy but can have other clinical manifestations and clinical overlap with MELAS.

This study focuses on MELAS which is progressive and life-limiting. Most individuals reportedly survive about 17 years [4] following the onset of symptoms such as seizures or other problems of the nervous system. There is an urgent need for the exploration of new treatment modalities to manage symptoms and improve the quality of life in people affected by MELAS. We aim to explore the notion that photobiomodulation (PBM; light therapy) activates mitochondria and relieves symptoms and signs of mitochondrial disease-related fatigue.

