## 3. Objectives

Our primary objective is to determine if combined red (660 nm), infrared (850 nm), and blue (465 nm) wavelengths of PBM applied using an array of multiple light emitting diodes (LED belt) is safe and reduces patient-reported fatigue as measured using the Checklist of Individual Strength (CIS) in people with MELAS.

The secondary objectives are as follows:

‐To determine if fatigue-related factors such as depression, anxiety, stress, and sleepiness are influenced by the application of PBM in people with MELAS.‐To determine if physical strength and activity changes in people with MELAS after PBM application to the large muscles of the lower limbs and the anterior abdomen.‐To determine if imaging using proton (^1^H) MR spectroscopy can show any change in mitochondrial activity in gastrocnemius muscles of the legs in people with MELAS.‐To determine if plasma creatine kinase (CK) and lactate are influenced by PBM application to the large muscles of the lower limbs and the anterior abdomen in people with MELAS.‐Based on outcomes, determine the feasibility of taking this research to the next phase as a larger clinical study.

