### 5.1. Limitations

As MR spectroscopy is expensive, our initial work is being done as a series of N-of-1 studies to establish the proof of concept. As a series of N-of-1 trials, it will not be possible to entirely exclude a placebo effect, but we have attempted to account for the effect by incorporating an initial sham phase into the study design. Equally, the small number of participants means the findings cannot be generalised. It is important to note that there are many statistical challenges related to N-of-1 trials including variability in patient responses, treatment-by-patient interactions, and missing data related to non-compliance with treatment. By maintaining weekly contact with participants, we expect to reduce the incidence of non-compliance with treatment.

The rationale we have taken for the choice in PBM parameters is based on a mix of theoretical underpinnings and published effects. In the absence of previous literature, dosing characteristics (duration and frequency of application, and duration of treatment protocol) are theoretical. The choice of the nominated red, blue, and NIR wavelengths is based on results from published in vitro and animal studies. Whether any of these factors translate into a human model of MD is unknown.

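### Safety is a primary aim, but the recording instruction leaves participants to judge what is unexpected, and the objective promises more than three participants can show

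*Protocol article*

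**What the plan says.** The primary objective (section 3) is to determine whether the combined-wavelength light belt "is safe and reduces patient-reported fatigue as measured using the Checklist of Individual Strength (CIS) in people with MELAS". The Abstract ranks the two parts slightly differently: "The primary outcome is patient-reported fatigue assessed using the Checklist of Individual Strength and with concomitant evaluation of safety".

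Section 4.4 sets out how safety is captured:

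- By diary: "participants will be asked to report/record in a study diary any unexpected effects (suspected side effects or adverse events) during the study".
- By asking: "We will ask participants about such matters at each assessment point".
- By open contact: "Participants will have contact details of the investigators should they experience effects of concern".

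Section 5.1 adds a regular contact, with compliance as its only stated purpose: "By maintaining weekly contact with participants, we expect to reduce the incidence of non-compliance with treatment".

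The Introduction describes the disease as presenting with "recurrent episodes of encephalopathy, myopathy with reduced exercise tolerance and fatigue, migraines, seizure disorder, and focal neurological deficits". Section 4.2 fixes the sample at three participants. Section 4.7 states that no power calculation was done and does not mention safety.

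**The concern.** The instruction is built on the word *unexpected*. The bracket explains that word, and the assessment-point questions pick up the same subject. Participants therefore have to decide for themselves whether something counts.

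That is a difficult judgement in MELAS. Someone who has lived with migraine, seizures or muscle symptoms may reasonably regard another episode as expected and leave it out, even if episodes have become more frequent or more severe. Yet a change in such events between the observation, sham and active phases is the safety signal that an A-B-A-C series could show. If these events are recorded unevenly, a report of no unexpected effects could coexist with a real worsening.

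The second strand is the objective. It promises to determine whether the treatment is safe, and three participants cannot support that conclusion even if nothing goes wrong.

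**Working it through.** **Recording instruction.** No arithmetic applies, so the texts are set side by side.

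1. Section 4.4 asks for "any unexpected effects (suspected side effects or adverse events) during the study". The noun is *effects*, the qualifier is *unexpected*, and the bracket glosses the phrase. One reading is that every adverse event is wanted. The other is that only adverse events the participant finds unexpected are wanted. The sentence does not settle which.
2. The assessment-point sentence refers back to the same matters, so it inherits the ambiguity.
3. The Introduction lists encephalopathy, myopathy, migraine, seizures and focal deficits as features of the disease. These are the events most likely to be judged expected.
4. The weekly contact in section 5.1 could resolve the ambiguity, but its stated purpose is compliance.

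**What three participants can show.** The document gives no safety figure to reproduce. The sample of three comes from section 4.2, and no target event rate is stated.

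For 0 events in n = 3, the exact binomial upper limit is 1 − α^(1/n):

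- One-sided 95%: 1 − 0.05^(1/3) = 0.632, or 63.2%.
- Upper end of a two-sided 95% interval: 1 − 0.025^(1/3) = 0.708, or 70.8%.

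The chance of seeing at least one affected participant is 1 − (1 − p)^3. The values of p are assumptions, chosen to show a range:

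| Assumed true risk per participant | Chance of at least one event in three | Chance of none |
|---|---|---|
| 5% | 14.3% | 85.7% |
| 10% | 27.1% | 72.9% |
| 20% | 48.8% | 51.2% |
| 30% | 65.7% | 34.3% |

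The true risk would have to be 1 − 0.2^(1/3) = 41.5% for an 80% chance of seeing even one event.

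**Exposure by phase** (section 4.1). Fourteen daily points in each of A, B and A give 2 weeks each, and C lasts 8 weeks. Per participant, that is 2 + 2 + 2 = 6 weeks without active light and 8 weeks with it. Over three participants it is 18 and 24 participant-weeks. If no event occurred in the 24 active participant-weeks, the one-sided 95% upper limit on the rate would be −ln(0.05)/24 = 0.125 per participant-week, assuming a constant rate.

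**Diary prompts.** The symptom diary is completed 14 times in 2 weeks (7 per week) in A and B, and 16 times in 8 weeks (2 per week) in C. If safety entries share that diary, which the article does not say, prompts are 7/2 = 3.5 times sparser during active light. This is a reason to ask one common question at a common interval.

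**The case against.** The strongest reply is that the text already covers the ground. Adverse events stand in the bracket as an item of their own, and on an ordinary reading a seizure during the study is one. There are other routes too:

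- Participants can contact the investigators about any effect of concern, expected or not.
- The Background section places the study under the supervision of the treating doctor.
- Muscle symptoms have their own measures: the fatigue and pain diary, creatine kinase and lactate, sit-to-stand and heel raises.
- Detailed adverse-event definitions may sit in the full protocol, which is not shown.
- The study calls itself exploratory, does no power calculation, and says its findings cannot be generalised.

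Much of this stands, and it rules out several stronger readings that a reader might infer:

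- **That only unexpected events are recorded.** The bracket makes exclusion possible, not demonstrated.
- **That known local effects of the belt are left out.** The article lists no such effects, so there is nothing to exclude.
- **That structured questioning happens only at assessment points.** The article does not call the questions structured. The diary runs throughout, and a compliance purpose for the weekly contact does not prove that safety is never raised there.
- **That nobody asks about safety during the 8 weeks of Phase C.** The assessment schedule is in Figure 1, which is not shown.
- **That the limit of three participants is concealed.** It is largely disclosed in sections 4.7 and 5.1.

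The reply does not dispose of the ambiguity in the stated instruction. The other routes are partial: contacting the investigators still depends on the participant judging an effect to be of concern, and the muscle measures do not capture migraine, seizures or focal deficits. Nor does limited generalisability say the same thing as the fact that zero events in three people cannot establish safety.

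**Conclusion.** The point holds as a matter of wording with practical consequences. The safety instruction is ambiguous about expected events. In a disease with recurrent episodes, that may lead to under-recording of worsening. The extent cannot be estimated from the document, and it depends on how participants read the sentence and on any fuller instructions they receive.

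The objective's wording outruns the design. No events in three participants would be compatible with a true risk of up to 63.2% (one-sided 95%) or 70.8% (upper end of a two-sided 95% interval), treating participants as independent with a common risk. An assumed 20% risk would go unseen with probability 0.512.

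This does not undermine the study as an exploratory series. It deserves correction because the change is nearly free and an unrecorded event cannot be recovered at analysis.

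**What to change.** 1. **Diary instruction (section 4.4).** Ask participants to record every adverse event and any worsening of MELAS symptoms, whether or not they expected it or think it related to the device.
2. **Same question throughout.** Put that question at the planned weekly contact in all four phases (A, B, A, C), and say in section 5.1 that the contact serves safety as well as compliance.
3. **Reporting.** List events descriptively by participant and phase with weeks of exposure (6 without active light, of which 2 are sham, and 8 with it). Note that the order is fixed (section 4.6), so phase is confounded with time and the list cannot attribute a difference to the light.
4. **Objective (section 3).** Replace the safety part with describing adverse events and tolerability. State that zero events in three participants would be compatible with a true risk of up to about 63% (one-sided 95%) or 71% (upper end of a two-sided 95% interval).

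The cost is a reworded diary line and one added question in a contact that already exists. The downside is more minor events to log and a more modest safety claim.

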## 4. Materials and Methods

### 4.1. Study Design

This study is an exploratory, prospective series of N-of-1 studies guided by the CONSORT extension for reporting N-of-1 trials (CENT 2015) [22]. We have chosen this method due to the rarity of MDs, their fluctuating symptomology, and the heterogeneity of clinical presentation. N-of-1 studies test the efficacy of an intervention using one or a small number of patients by sequentially applying and withdrawing the intervention [23]. The simplest of such study designs is an A-B-A design where A is ‘no treatment’ and B is the intervention being studied. Continuous measurement of chosen outcomes occurs through each of the stages.

The PBM parameters will be standardised in all study participants, following an A-B-A-C design (Figure 1) as follows:
‐A = no intervention observational period: Daily patient diary (visual analogue scale; VAS) of fatigue and pain to understand usual (baseline) behaviour of fatigue and pain symptoms, to compare with any change during/after intervention. Fourteen data points will be obtained in each non-intervention period. In this study, the repeated “A” period will also serve as a washout period after the sham phase, to account for any placebo response.‐B = sham intervention period: Daily patient diary (VAS) of fatigue and pain symptoms will be assessed. Fourteen data points will be obtained. We have included a sham phase in this series of N-of-1 trials to satisfy the requirement to understand if there may be a placebo element to the initial application of light. To reduce the burden on participants, we have chosen a 2-week sham period which is expected to demonstrate any change from baseline. The following A phase will assist in determining the durability of any placebo effect that we may need to consider in a future study.‐C = active intervention (PBM application) period: Twice-weekly patient diary of fatigue and pain symptoms will be assessed. Sixteen data points will be obtained over an 8-week period of treatment. The intervention period is based on exercise science findings demonstrating increased mitochondrial activity with endurance exercise [24] and mitochondrial biogenesis after 4–6 weeks of interval training in healthy individuals [24,25]. If PBM influences muscle mitochondrial function, we expect that 8 weeks of home-based intervention may be required to demonstrate effects in a clinical population that would normally struggle to participate in exercise programs.

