MR spectroscopy will be conducted four times as indicated in Figure 1. The MRS scan at time point 2 (after the initial 2-week observational Phase A) will be a baseline measure to establish the participant’s ‘usual’ level of target factors. A second and third MRS scan will be undertaken at the commencement of the active intervention Phase C. The second MRS scan will be taken immediately before the first active PBM treatment. The MRS will be followed by a 10-min PBM treatment of the calf muscles in a room adjacent to the MR scanner. The third MRS scan will be undertaken as soon as possible after the PBM treatment to determine if there is an ‘acute’/immediate change in mitochondrial activity signal following the treatment. After the completion of Phase C, the 8-week at-home self-applied PBM treatment, the final MR spectroscopy will be undertaken to determine if there is a longer-term change/response in mitochondrial activity signal and by how much (reflecting the rationale that light stimulates mitochondrial activity durability and biogenesis).

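### Blood lactate, CK and MRS lactate are never sampled under sham, so the sham phase does not control them and a Phase C change cannot be attributed to PBM

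*Protocol article*

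**What the plan says.** **Phases.** Section 4.1 sets the sequence: "following an A-B-A-C design (Figure 1) as follows". A is observation, B is sham and C is active PBM. On the sham phase it says: "we have chosen a 2-week sham period which is expected to demonstrate any change from baseline". Of the second observation phase it says "the repeated “A” period will also serve as a washout period after the sham phase". For Phase C: "Sixteen data points will be obtained over an 8-week period of treatment". Section 4.6 confirms that the order is not randomised.

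**Blood lactate and CK.** Section 4.4: "Blood tests will be required on three occasions, at intake to the study and at the start and end of active intervention Phase C".

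**MRS lactate.** Section 4.5 plans four scans. The first: "The MRS scan at time point 2 (after the initial 2-week observational Phase A) will be a baseline measure". Then: "A second and third MRS scan will be undertaken at the commencement of the active intervention Phase C", one just before the first active application to the calves and one as soon as possible after it. The last follows Phase C.

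**What is to be concluded.** Section 3 asks whether CK and lactate are affected by PBM. Section 4.4 intends the blood tests to show response to the intervention. Section 4.5 would take a fall in MRS lactate as evidence that PBM raises mitochondrial activity. Section 4.7 plans descriptive statistics and explores pre-post effects for Phase C only. Section 5.1 concedes that placebo cannot be fully excluded and adds: "we have attempted to account for the effect by incorporating an initial sham phase into the study design".

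**The concern.** A sham phase controls only those endpoints that are measured in it. Section 4.1 itself describes N-of-1 studies as following outcomes throughout every stage, but the blood and MRS markers skip the sham stage. Their first value after sham comes two weeks later, at the end of a phase meant to let any sham response fade.

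Expectation is not the only issue. Lactate and CK can move with activity, with rest during application, and with the fluctuation that section 4.1 gives as a reason for choosing the N-of-1 design. The acute pair is exposed in its own way: two resting scans are separated by a ten-minute application, and no equivalent pair is taken with the inactive device to show what rest and repeat scanning do to the signal.

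At stake is the mechanistic conclusion. Section 6 says that the results will help decide whether to proceed to further research and how to design it. A lactate fall read as a PBM effect would enter that decision with no sham comparison behind it.

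**Working it through.** **Inputs.** Phase order, the 2-week sham and the 8-week active phase come from section 4.1. Each observation phase is 2 weeks: fourteen daily diary points give 14 ÷ 7 = 2. Sampling occasions come from sections 4.4 and 4.5.

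**Timeline check.** The plan's own diary counts reproduce: 2 weeks × 7 days × 1 = 14 points for A and B; 8 weeks × 2 per week = 16 points for C.

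**Timeline.** First A, weeks 0–2; sham B, weeks 2–4; second A, weeks 4–6; active C, weeks 6–14.

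| Marker | Occasions (week) | Within or at end of B (after week 2, up to week 4) |
|---|---|---|
| Blood lactate, CK | 0, 6, 14 | 0 of 3 |
| MRS lactate | 2, 6 (before treatment), 6 (after treatment), 14 | 0 of 4 |

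The week-2 scan lies on the boundary between A and B, but the text defines it as the pre-device baseline, so it is not a sham value.

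**Intervals between successive values.**
- Blood, pre-active: 6 − 0 = 6 weeks (2 observation + 2 sham + 2 washout).
- MRS, pre-active: 6 − 2 = 4 weeks (2 sham + 2 washout).
- Both, active: 14 − 6 = 8 weeks, which is 8 ÷ 2 = 4 times the length of sham.

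**What can be computed.** A sham change needs a value at the start and at the end of B. No end-of-B value exists for either marker, so no analysis can recover the change. What remains is the pre-active change (start of C minus the earlier value) and the Phase C change (end of C minus start of C). The pre-active change contains sham but ends 2 weeks after it, so sham effect, its decay and background change cannot be told apart. Both changes also share the start-of-C value: a chance high reading there produces a rise followed by a fall.

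**Acute pair.** Both scans are at week 6, around active treatment. Number of matching pairs around sham treatment: 0.

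**The case against.** **Exploratory study, placebo already conceded.** Section 5.1 says that MRS is expensive, that the aim is proof of concept and that placebo cannot be ruled out. Section 4.4 ties the secondary measures to feasibility, and section 4.7 plans descriptive analysis and doubts that pre-post effects can be measured. This stands as a reason not to demand more scans. It does not cover the causal reading of a lactate fall in section 4.5, and section 5.1 offers the sham phase as mitigation without excepting these markers.

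**Leave it to the analysis plan.** Sampling times are fixed in this document, and no later analysis can create an end-of-sham value.

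**Stronger readings that a reader might infer.**
- *That every objective endpoint lacks a sham comparator.* The text does not support this. Sit-to-stand and heel raises are tested on five occasions, and step counts are collected in every phase if the participant has a device. Section 6 calls the physical outcomes objective. The sequence has five phase boundaries (weeks 0, 2, 4, 6, 14), so one physical test probably falls at the end of sham. That is an assumption, because Figure 1 is not shown.
- *That nothing can be learned about drift.* Each marker has two values before active treatment, which give a crude within-person look at fluctuation. With two points, sham mixed in and three participants, that look cannot establish a trend.
- *That the intake draw and the time-point-2 scan should be moved to the end of sham.* This would remove the protocol-timed pre-sham value, so a sham change still could not be computed. It would also lose the only scan taken before any device use, and any record value substituted for intake blood would have an uncontrolled date. Neither move would give the acute pair a sham counterpart.

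**Conclusion.** The point holds for blood lactate, CK and MRS lactate, and for those markers only. Per participant, 0 of 3 draws and 0 of 4 scans are informative about sham, and the acute pair has no sham pair. The sham phase therefore does not do for these endpoints what section 5.1 suggests, and a Phase C or acute change cannot be assigned to PBM over device routine, rest or fluctuation.

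This is a fault of interpretation and reporting within a defensible low-cost schedule. It does not touch diary fatigue and pain, which are recorded during sham.

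The counts rest on three assumptions: intake coincides with the start of the first Phase A, the phases follow without gaps, and the start-of-C draw precedes the first active treatment. A gap between phases would lengthen the pre-active intervals but would not create an end-of-sham value.

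**What to change.** Leave the sampling schedule unchanged.

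1. **Sections 4.4, 4.5 and 5.1:** state that blood lactate, CK and MRS lactate are not measured under sham and are not sham-controlled. In 4.5, replace the inference from decreased lactate to a PBM effect with uncontrolled pre-post description, explicitly including the scans before and after the first active treatment.
2. **Section 4.7:** for each participant, report the pre-active change (blood: intake to start of C, 6 weeks; MRS: time point 2 to the pre-treatment scan at start of C, 4 weeks) beside the 8-week Phase C change. Note that the intervals differ in length, that the pre-active interval mixes sham and washout, and that both changes share the start-of-C value.

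The cost is a few sentences and one extra column in the results. No draw or scan is added, moved or lost. The price is a weaker claim from these markers, which is all that the schedule can support.
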